## Abstract

**Background:**

Poststroke epilepsy poses a significant clinical challenge for individuals recovering from strokes, leading to a less favorable long-term outlook and increased mortality rates. Existing studies have primarily concentrated on administering antiseizure or anticonvulsant treatments only after the onset of late-onset seizures, without intervening during the epileptogenesis phase following a stroke.

**Objective:**

This research protocol is designed to conduct a randomized controlled trial to assess whether the early, preventive introduction of low-dose antiepileptic drug therapy (levetiracetam [LEV] or perampanel [PER]) in patients who have experienced middle cerebral artery (MCA) infarction can reduce the risk of developing poststroke epilepsy (primary prevention).

**Methods:**

Participants with MCA infarction, either with or without reperfusion treatments, will be recruited and promptly receive preventive intervention within 72 hours of the stroke occurrence. These participants will be randomly assigned to receive either PER (4 mg per day), LEV (1000 mg per day), or a placebo that matches the active drugs. This treatment will continue for 12 weeks after allocation. Brain magnetic resonance imaging will be used to confirm the presence of MCA territory infarction, and an electroencephalography will be used to ensure the absence of epileptiform discharges or electrographic seizures at the time of the stroke. All participants will undergo follow-up assessments for 72 weeks after allocation.

**Results:**

The primary outcome under evaluation will be the incidence of poststroke epilepsy in the 3 groups following the 18-month study period. Secondary outcomes will encompass the time to the occurrence of the first seizure, the severity of seizures, any treatment-related adverse events, and the modified Rankin scale score at 3 and 18 months. Exploratory outcomes will involve comparing the effectiveness and safety of PER and LEV.

**Conclusions:**

We anticipate that the intervention groups will experience a lower incidence and reduced severity of poststroke epilepsy compared to the control group after 18 months. We aim to establish evidence supporting the potential preventive effects of LEV and PER on poststroke seizures and epilepsy in patients with MCA infarction, as well as to explore the antiepileptogenic potential of both LEV and PER in patients with major ischemic strokes.

**Trial Registration:**

ClinicalTrials.gov NCT04858841; https://clinicaltrials.gov/study/NCT04858841

**International Registered Report Identifier (IRRID):**

DERR1-10.2196/49412

## Introduction

### Background

Advances in stroke treatment have caused a considerable reduction in stroke mortality; however, the number of stroke survivors living with disability has increased significantly. Seizures and epilepsy related to ischemic stroke are common, and poststroke epilepsy is a significant clinical problem for stroke survivors. Stroke is the most common cause of epilepsy in older adults and for patients older than 65 years of age, and poststroke epilepsy accounts for 30%-50% of new-onset seizures [1]. The incidence of early seizures (occurring within the first 1-2 weeks of stroke) is 2.4%-5.4%, and the risk of poststroke late seizures (seizures occurring later than after 14 days of stroke) is approximately 7%-18% [1,2]. Late-onset poststroke epilepsy has a higher recurrence rate of up to 71.5% within 10 years after stroke [3]. Our previous study demonstrated that seizures during stroke increase overall morbidity and mortality [4]. The stroke severity, location (for example, middle cerebral artery [MCA] infarcts in our study), and the type of pathological changes, genetic factors, and pre- and postinjury exposure to nongenetic factors influence the susceptibility of patients with ischemic stroke [5,6]. The standardized morbidity rate of developing epilepsy is highest during the first year after stroke. In addition, higher National Institutes of Health Stroke Scale (NIHSS) score [7], cortical involvement, younger age, and central nervous system morbidities are associated with higher risk of poststroke epilepsy [1,8].

The effects of thrombolysis and thrombectomy on long-term poststroke epilepsy remain unclear. A retrospective evaluation of patients with thrombolysis found that 4% developed poststroke seizures during hospitalization and that death during admission was significantly more likely in those with seizures compared to those without seizures [9]. Another study found that 5.5% of patients receiving endovascular therapy had seizures between stroke onset and 3-month follow-up, and early seizures independently predicted a significantly unfavorable outcome [10]. Regarding early postthrombectomy seizures, 2.4% of patients with ischemic stroke treated with thrombectomy developed at least 1 seizure within 7 days of stroke onset, and the occurrence of seizures was associated with higher 90-day mortality and poorer functional outcomes [11]. For patients with stroke, receiving reperfusion treatments was not associated with acute symptomatic poststroke seizures or poststroke epilepsy [7,12].

Ethnicity may be an important factor in the development of poststroke seizures and epilepsy. The prevalence of poststroke seizures in patients without atrial fibrillation is higher in Australia than in China [13]. In Taiwan, 1 study found that atrial fibrillation may cause ischemic stroke that subsequently causes seizure and atrial fibrillation is associated with a higher rate of subsequent seizure [14]. One-year poststroke epilepsy risk is higher in patients staying in the ICU or in patients with seizure at stroke admission, atrial fibrillation, or cognitive impairment [15]. Late poststroke seizure recurrence is more common in patients of young age (younger than 65 years of age), of male sex, with large lesion seizure, or with partial-onset seizure [16].

### Concept of Epileptogenesis

Antiepileptic drugs (AEDs) or antiseizure medications may prevent the recurrence of seizures but do not cure epileptogenesis. An epileptogenesis is the process by which the previously normal brain is functionally altered and biased towards the generation of abnormal electrical activity that induces chronic seizures [17]. It involves molecular, anatomical, or circuit-level alterations, such as cell death or dysregulation of an ion channel or neurotransmitter receptor and the impairment of intrinsic plasticity. How these different levels of alteration are regulated remains unclear. Studies have reported that the epigenetic factor chromodomain Y-like protein, a critical regulator of the initiation and maintenance of intrinsic neuroplasticity that works by regulating voltage-gated sodium channels [18], is involved, and epileptic neurons may also develop short- and long-term adaptive changes in sensitivity to gamma-aminobutyric acid (GABA)ergic neurotransmission [19], worsening excitatory or inhibitory imbalance and thus reducing the possibility of successful therapeutic approaches using traditional AEDs. Further, an increasing amount of research, including ours, suggests a major involvement of inflammation in epileptogenesis [20-22]. Seizure activity elicits the release of proinflammatory cytokines and activates immune responses.

We have studied medications with potential antiepileptogenesis effects in pilocarpine-induced seizure animal models, supporting the concept of antiepileptogenesis with intervention immediately following brain insult [21-23].

### Studies Regarding Primary Prevention

The clinical trials aimed at the prevention of chronic epilepsy have often produced negative results because they mainly evaluated downstream clinical manifestations instead of monitoring early, specific molecular epileptogenic events and applying early intervention. A 1990 study on primary prevention of posttraumatic seizures with early use of phenytoin [24] indicated that phenytoin exerts a beneficial effect by reducing seizures only during the first week after severe head injury.

American Heart Association guidelines indicate that prophylactic AEDs are not recommended for the prevention of poststroke seizure [25] due to the lack of randomized control trials and some reports indicating that prophylactic AED therapy may be associated with poorer outcomes [26-28]. In addition, valproic acid therapy was found to be ineffective compared with a placebo in preventing the occurrence of late-onset seizures in patients with spontaneous and nonaneurysmal intracerebral hemorrhage [29]. Nevertheless, the lack of success in prophylactic AED therapy trials may be related to the use of traditional AEDs.

### Medications With Antiepileptogenetic Potential

Numerous AEDs exist. Based on our clinical experience and laboratory research [21,22,30-33], we have identified 2 newer AEDs with antiepileptogenesis potential. Levetiracetam (LEV), which exhibits a distinct synaptic vesicle modulating mechanism, has exhibited the potential in ameliorating epileptogenesis [1,34,35]. Our earlier research indicates that it has a broad spectrum of modulating neuronal excitability [30]. It exhibits no clinically relevant drug-drug interactions [36]. Perampanel (PER), a standard AED with a distinct mechanism of selective noncompetitive antagonism of alpha-amino-3-hydroxy-5-methyl-4-isoxazolepropionic acid (AMPA)-type receptors, is also effective in treating a wide spectrum of epileptic seizures and has a favorable tolerability profile [37]. Because it blocks glutamate excitotoxicity, PER is theoretically capable of modulating epileptogenesis and has demonstrated potential in ameliorating epileptogenesis [32,38,39]. Thus, it is potentially justified to evaluate whether early prophylactic administration of LEV or PER in patients with acute major stroke hampers the development of epileptogenesis and later poststroke epilepsy.

## Methods

### Overview

We will conduct a prospective randomized, triple-blind, and placebo-controlled study. To calculate the appropriate sample size, we took into account various factors including the population size, margin of error, confidence level, expected variance, number of patients with MCA infarcts admitted to our medical center annually, and potential loss rate. We used G*Power software (Heinrich-Heine-Universität Düsseldorf) to perform these calculations. Specifically, we used an effect size ranging from 0.25 to 0.4, α error probability of .05, power of 0.5, 3 groups, 2 measurements, and a correlation of 0.05 between repeated measures. The resulting total sample size ranged from 51 to 120. Based on the potential number of patients admitted to our medical center and the expected loss rate, we estimated that enrolling 180 cases would be reasonable.

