### Randomization and Blinding

Block randomization of eligible participants will be performed to form the LEV, PER, and placebo groups. Blinding of participants, clinicians, and data collectors will be performed so that these individuals do not have access to group assignment details (Figure 2). Before accepting the case, the pharmacist, who is a nonresearch team member, sets the blocks and determines the distribution of random numbers using a random number table. The pharmacist is responsible for conducting all phases of the research. Additionally, the 3 topic groups can be equally distributed among participants through random assignment.

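### The printed G*Power inputs (power 0.5, correlation 0.05) do not give the printed total of 51 to 120 in any ANOVA module tried

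*Protocol article*

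**What the plan says.** The sample-size statement is in the protocol article, Methods, Overview. It names the program ("We used G*Power software") and gives the effect size ("we used an effect size ranging from 0.25 to 0.4") and the significance level ("α error probability of .05"). The remaining inputs are "power of 0.5, 3 groups, 2 measurements, and a correlation of 0.05 between repeated measures". The result follows: "The resulting total sample size ranged from 51 to 120". The article then moves from this range to its target on the basis of admissions to the centre and expected losses: "we estimated that enrolling 180 cases would be reasonable".

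The G*Power module is not named. Groups, measurements and a correlation between measurements are together the inputs of the repeated-measures ANOVA family. Allocation is meant to be equal (Randomization and Blinding: "the 3 topic groups can be equally distributed among participants through random assignment"), so the total moves in steps of 3. No other part of the article restates or corrects the power or the correlation.

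**The concern.** The article prints every numeric input and the output, so the result can be checked without a fuller protocol or an SAP. A power of 0.5 is unusual for a planned trial, and a correlation of 0.05 between two measurements on the same patient is unusually low. With power that low, a total of 120 at an effect size of 0.25 looks too large.

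This sentence is the article's only quantitative support for the sample size. If the inputs are misprinted, readers are told that the trial was planned with an even chance of missing its target effect when it was not. If the inputs are right, the printed range is wrong. In both cases the range cannot be verified from what is printed.

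**Working it through.** **Inputs (Methods, Overview).** Cohen's f = 0.4 and 0.25; alpha = 0.05; target power 0.5; k = 3 groups; m = 2 measurements; correlation rho = 0.05. N is the total and rises in multiples of 3.

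**Method.** Power is the probability that a noncentral F variable with noncentrality lambda exceeds the central F critical value at alpha. The required N is the smallest multiple of 3 that reaches the target power.

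- Between factors: lambda = f² × N × m / (1 + (m − 1) × rho), df = k − 1 and N − k.
- Within factors and within-between interaction: lambda = f² × N × m / (1 − rho). The numerator df is m − 1 (within) or (k − 1)(m − 1) (interaction); the denominator df is (N − k)(m − 1).
- Effect size as in Cohen, and one-way ANOVA: lambda = f² × N.
- Effect size as in SPSS: lambda = f² × (N − k) × (m − 1).

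**Step 1: try to reproduce 51 to 120 from the printed inputs.**

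| Module | N at f = 0.4 | N at f = 0.25 | 51 / N | 120 / N |
|---|---|---|---|---|
| Printed in the article | 51 | 120 | | |
| Between factors | 21 | 45 | 2.4 | 2.7 |
| Within-between interaction | 21 | 42 | 2.4 | 2.9 |
| Within factors | 15 | 33 | 3.4 | 3.6 |
| Within factors, as in Cohen | 27 | 66 | 1.9 | 1.8 |
| Within factors, as in SPSS | 30 | 69 | 1.7 | 1.7 |
| Interaction, as in Cohen | 36 | 84 | 1.4 | 1.4 |
| Interaction, as in SPSS | 39 | 87 | 1.3 | 1.4 |
| One-way ANOVA | 36 | 84 | 1.4 | 1.4 |

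No row gives 51 and 120. As an example, take between factors at f = 0.25. N = 45 gives lambda = 0.0625 × 45 × 2 / 1.05 = 5.36 and power 0.503, while N = 42 gives lambda = 5.00 and power 0.472. So 45 is the smallest qualifying total.

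**Step 2: power at the printed totals (between factors, rho = 0.05).**

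- N = 51, f = 0.4: lambda = 0.16 × 51 × 2 / 1.05 = 15.54, power 0.94.
- N = 120, f = 0.25: lambda = 0.0625 × 120 × 2 / 1.05 = 14.29, power 0.93.

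Neither is near 0.5.

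**Step 3: look for inputs that do give the printed range (between factors, alpha 0.05).**

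| Power | rho | N at f = 0.4 | N at f = 0.25 |
|---|---|---|---|
| 0.80 | 0.05 | 36 | 87 |
| 0.5 | 0.5 | 27 | 63 |
| 0.80 | 0.5 | 51 | 120 |

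Changing only one of the two inputs to these values is not enough. With both changed, the two ends match exactly. At f = 0.4, N = 48 gives power 0.797 and N = 51 gives 0.824. At f = 0.25, N = 117 gives 0.794 and N = 120 gives 0.805.

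**Step 4: is that match unique?** No. On a between-factors grid with power in steps of 0.01 and correlation in steps of 0.05, 15 pairs give exactly 51 and 120. Besides 0.80 with 0.5, they include 0.75 with 0.70, 0.83 with 0.40 and 0.90 with 0.15. The interaction module at power 0.95 and rho = 0.05 comes close, with 51 and 123. One-way ANOVA at power 0.5 gives 51 and 120 if alpha is .05/3, but the article states .05.

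**The case against.** The strongest reply is that nothing operational depends on this sentence. Enrolment was set at 180 from admissions and expected losses, and 180 exceeds both the printed range and every total recomputed from the printed inputs. That stands: the correction changes no target, analysis or decision, and its weight is that of a reporting correction.

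A second reply is that, with the module unnamed, nobody can say what the printed inputs should have given. This stands in part. A reader might take 21 to 45 as the right answer, but that holds only for between factors with the default effect-size definition. With the SPSS definition for the interaction, the gap shrinks to about 1.3 to 1.4 times. The missing name does not remove the contradiction, however, because no module tried reaches 51 and 120.

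A third reply is that the match at power 0.80 and correlation 0.5 is a back-calculation. A reader might infer that these must be the values used. The article does not support that, since several other pairs fit equally well. The case for 0.80 and 0.5 is that both are conventional values; that is a matter of plausibility and not proof.

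A reader might also infer from the printed 0.5 that the trial was planned with 50% power. That cannot be concluded either, because the printed totals do not correspond to power 0.5 in any module tried.

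**Conclusion.** The point holds as an internal contradiction: the printed inputs and the printed total in the Methods overview cannot both be right. The printed range is about 1.3 to 3.6 times too large for the stated inputs, depending on the module, and 2.4 to 2.7 times if the module was between factors. The result assumes an omnibus F test at alpha .05, equal groups, and the ANOVA modules and effect-size definitions listed in the working.

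Power 0.80 with correlation 0.5 in the between-factors module is the most plausible source, and only the authors' G*Power output can confirm it. The finding does not show that 180 is too few or too many. It also leaves open whether an ANOVA effect size suits an incidence outcome. That is a separate question, and correcting this sentence would not answer it.

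**What to change.** Retrieve the G*Power output and name the module and effect-size definition in the sample-size sentence. Then make one of two corrections:

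- If the output shows other values, print the power and correlation actually used, so that they yield 51 to 120 (0.80 and 0.5 if the output confirms them).
- If power 0.5 and correlation 0.05 really were entered, replace the range with the one for the module used (21 to 45 if between factors).

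The cost is one file to check and one sentence to correct. The enrolment target of 180 and the conduct of the trial are unaffected.

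### The sample size is calculated for repeated continuous measurements, but the main primary outcome is one yes/no epilepsy status per patient, and the printed inputs do not give the printed range

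*Protocol article*

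**What the plan says.** The Methods, Overview, describe a G*Power calculation: "we used an effect size ranging from 0.25 to 0.4", with "α error probability of .05, power of 0.5, 3 groups, 2 measurements, and a correlation of 0.05 between repeated measures". The reported result is: "The resulting total sample size ranged from 51 to 120". The final number is then chosen from expected admissions and a loss rate for which no figure is given: "we estimated that enrolling 180 cases would be reasonable". No placebo risk, target risk or risk difference enters the calculation.

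The Abstract (Results) defines the endpoint: "The primary outcome under evaluation will be the incidence of poststroke epilepsy in the 3 groups following the 18-month study period". The Primary Outcome section lists seizure severity beside incidence and plans a univariate ANOVA of the three groups. The Secondary Outcomes section lists severity again as secondary. The Statistical Analysis section assigns nominal variables to chi-square or Fisher tests.

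The only event rates are in the narrative. The Background states that "the risk of poststroke late seizures (seizures occurring later than after 14 days of stroke) is approximately 7%-18" per cent. The Discussion cites annual risks after a first ischemic stroke of 6.3% in year 1 and 2.4% in year 2.

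**The concern.** Two measurements and a correlation between them have no counterpart in an outcome that each patient either has or does not have at 18 months. The planned primary analysis, a univariate ANOVA, has no repeated factor either. The effect size therefore has no clinical meaning until it is converted to risks, and the article does not convert it.

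A reader who takes 180 as comfortably above a required 51 to 120 will believe that the trial has power to spare. If its power for incidence is low, a null result is the likely outcome even when both drugs work, and it could be misread as evidence against prevention. The printed power of 0.5 adds a second difficulty: it is unclear what power the authors meant to claim.

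**Working it through.** **1. Reproducing 51 to 120.** The test is not named; the inputs are those of G*Power's repeated-measures ANOVA. For the between-groups test with k = 3 groups and m = 2 measurements, the noncentrality is λ = f²·N·m / (1 + (m − 1)ρ), with 2 and N − 3 degrees of freedom. N is rounded up to a multiple of 3.

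| Inputs | f = 0.25 | f = 0.4 |
|---|---|---|
| As printed: power 0.5, ρ = 0.05 | N = 45 (λ = 5.36, power 0.503) | N = 21 (λ = 6.40, power 0.537) |
| Power 0.80, ρ = 0.5 | N = 120 (λ = 10.00, power 0.805) | N = 51 (λ = 10.88, power 0.824) |
| Article reports | 120 | 51 |

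With the printed inputs, the within-groups test gives 33 and 15 and the interaction test 42 and 21. None gives the printed range. The second row matches both ends exactly. The interaction test at power 0.95 and ρ = 0.05 comes close (123 and 51).

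**2. The effect size as risks.** For proportions, f is the standard deviation of the three group risks divided by √(mean of p(1 − p)). With placebo risk p and risk q in both active arms, the numerator is (p − q)·√2/3.

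- Halving 18%: 0.0424 / √0.1038 = 0.132. Halving 7% gives 0.078.
- f = 0.25 from 18%: q = 3.7%, since 0.0675 / √0.0728 = 0.250.
- Largest possible f (q = 0): √(2p / (3(1 − p))). This is 0.224 at p = 7% and 0.383 at p = 18%.
- Solving for p: f = 0.25 cannot be reached below p = 8.6%, and f = 0.4 needs p of at least 19.4% with no events on either drug.

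Halving therefore corresponds to f of 0.08 to 0.13, about half or less of the smallest value used.

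**3. Power for incidence at 180.** Inputs: 60 per arm (equal allocation), two-sided 0.05, no losses; placebo risk 7%, 12.5% (midpoint) and 18%, with 30% as an illustration; equal reduction in both active arms. The reductions are assumptions, because the article states none. The three-group power sums exact binomial probabilities over the chi-square rejection region. The pairwise power is Φ{(|p₁ − p₂| − 1.96√(2p̄(1 − p̄)/60)) / √((p₁(1 − p₁) + p₂(1 − p₂))/60)}. For 18% against 9% this is Φ{(0.09 − 0.1223)/0.0618} = Φ(−0.52) = 30%.

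| Placebo risk | Reduction | Three-group chi-square | Each drug vs placebo |
|---|---|---|---|
| 7% | 50% | 13% | 13% |
| 12.5% | 50% | 22% | 21% |
| 18% | 50% | 32% | 30% |
| 30% | 50% | 55% | 50% |
| 18% | 75% | 74% | 65% |
| 7% | 100% | 80% | 55% |

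**4. Detectable risk and precision.** Against 18% placebo, 80% power needs an active risk of about 2.6% pairwise (86% reduction) or about 3.9% in both arms on the three-group test (78% reduction). The 95% confidence interval half-width for a risk difference is 1.96 × 0.0618 = 12 points for 18% against 9%, and 8 points for 7% against 3.5%. Both exceed the differences themselves (9 and 3.5 points).

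**The case against.** **Only 50% power was printed.** True, and at an assumed 30% risk halving reaches it. But halving falls short of 50% throughout 7% to 18%, and the printed 0.5 does not produce the printed range.

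**The placebo risk may be higher.** The 7% to 18% is a general ischemic-stroke figure. The trial enrols MCA infarcts with an NIHSS score above 8, and the Background names severity, cortical involvement and MCA location as factors that influence risk. This stands: the placebo risk is an assumption, and the larger effect sizes cannot be ruled out. The Discussion's annual risks point the other way: 6.3% plus half of 2.4% is about 7.5% at 18 months.

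**The effect may exceed halving.** It may; the table shows a 75% reduction from 18%, which still misses 80% before losses.

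**Severity is also listed as primary.** It is in one section, so the binary description is exact only for incidence. But the Abstract names incidence alone, the objective concerns the risk of developing epilepsy, and the article plans no two-measurement analysis of severity.

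**The second measurement is not the main fault.** Correct. A one-way ANOVA with 180 patients would have 85% power at f = 0.25. The unconverted effect size drives the shortfall.

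**The size is set by feasibility.** That is legitimate and partly stated. The conclusions are also hedged: they speak of a potential effect. A reader might infer a promise of definitive proof, which the wording does not support.

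**Conclusion.** The point holds. The sample size paragraph uses a calculation that does not fit the incidence outcome, and its printed inputs contradict its printed result. With halving assumed and a placebo risk of 7% to 18%, power at 60 per arm without losses is 13% to 32% (three groups) or 13% to 30% (pairwise). That is below both the printed 50% and the 80% that reproduces 51 to 120.

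Three stronger readings go too far. First, a reader might infer that no effect could be detected with 80% power at a 7% placebo risk. That is true of a pairwise comparison (55% with no active events) but not of the three-group test, which just reaches 80% in that extreme case. Second, a reader might infer that the authors intended 80% power. The exact match makes this likely, but the article prints 0.5 and the source of the mismatch is not known. Third, a reader might infer that the trial is too small to be worth running or must be enlarged. The article states neither a target effect nor a placebo risk for its own population, so it cannot settle that. What it does show is that 180 has not been justified for the incidence outcome.

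**What to change.** Replace the G*Power paragraph with a calculation for the incidence of poststroke epilepsy at the planned 180 patients. State:

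- the assumed placebo risk and its source, with a range;
- the target effect as a risk or risk reduction;
- the comparison or comparisons to which the power applies (three-group, or each drug against placebo);
- the loss rate as a figure;
- the resulting power, the detectable active risk and the confidence interval half-width.

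Correct or remove the power of 0.5, the correlation of 0.05 and the range 51 to 120. Say openly that feasibility fixed the number, if that is so. Add to the conclusions that a non-significant result will not be read as absence of a preventive effect.

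The cost is one rewritten paragraph and one added sentence. No extra patients are needed. The downside is that the stated power becomes less favourable.
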